## Abstract

**Background:**

The bioethical principle of respect for patients' autonomy should be implemented in every area of health care. The German rehabilitation system has some characteristics (e.g. the prevalence of inpatient rehabilitation) that make the topic particularly relevant. The aim of the study is to determine the current state of respecting patient autonomy in inpatient medical rehabilitation in Germany and to identify barriers and promoting factors from the perspective of relevant groups.

**Methods:**

A multi-center, prospective, cross-sectional study is being conducted, including interviews with patients (*n* = 24), interviews with professionals (*n* = 21) and a survey of medical directors (*n* = 900). The empirical findings are then reviewed in three validation workshops. In addition, consensus recommendations for practice are derived by means of a Delphi process with experts (*n* = 30).

**Discussion:**

This study will address an important gap in the empirical literature by identifying the current state and needs of patients, professionals and medical directors of rehabilitation clinics regarding the practice of respecting patient autonomy in inpatient medical rehabilitation in Germany. It is expected that the results can contribute to coming closer to the ideal of respect for patient autonomy in rehabilitation practice.

**Trial registration:**

The study was registered with the German Clinical Trials Registry (ID: DRKS00035893).

## Background

Medical rehabilitation is an important part of healthcare at various stages of life if there is a risk of or already existing health-related impairment to social and occupational participation [1]. In Germany, medical rehabilitation mainly takes place on an inpatient basis, where patients usually spend a period of at least 3 weeks. Also, rehabilitation clinics in Germany are highly specialized and focus on specific diagnostic groups. Medical fields in which inpatient medical rehabilitation most frequently take place are (in order of frequency): orthopedics, psychosomatics/psychotherapy, oncology, cardiology, neurology, and internal medicine [2]. Due to the availability of specialized clinics, the rehabilitation stay is often outside of the patients´ hometown [3]. In 2023, there were over 1.000 rehabilitation clinics with more than 161.000 beds in Germany. The size of the clinics varies from 30–40 beds up to clinics with over 500 beds. The average patient occupancy rate in 2023 was 81.5% [4]. In the rehabilitation clinics, interdisciplinary teams encompass various professionals (e.g. rehabilitation physicians, physiotherapists, occupational therapists, nutritionists, psychologists) with a strong medical dominance [3]. In Germany, inpatient medical rehabilitation is financed either by the German Pension Insurance, the statutory health insurance or an accident insurance [5]. For people of working age (usually 18–67 years old), inpatient medical rehabilitation is typically financed by the German Pension Insurance. This is the case for up to two thirds of all rehabilitation procedures [6]. Almost 1.5 million rehabilitation applications were submitted to the German pension insurance in 2022 [2].

Respect for the autonomy of patients is one of the guiding bioethical principles [7]. Structures, institutions and professionals in all areas of health care are obliged to respect the autonomy of patients. The research project „[blinded for peer review]“ focuses on the autonomy of patients in inpatient medical rehabilitation in Germany.

In Sec. 1 of the German Social Code IX, self-determination is declared as a primary goal and a relevant outcome of all rehabilitation measures in Germany. In its framework, the German Pension Insurance also names self-determination and participation as overarching goals of rehabilitation [8]. Preserving and promoting the autonomy of patients in rehabilitation can be an important element in achieving these goals [9]. The principle of respecting autonomy is particularly relevant for patients in medical rehabilitation, as measures during the rehabilitation stay can intervene deeply in the physical and psycho-emotional sphere of those affected. Institutional aspects can also be significant, as medical rehabilitation in Germany is predominantly carried out on an inpatient basis [2]. Chronic illnesses, which are often treated in inpatient medical rehabilitation, are often associated with autonomy-related impairments, which makes respect for patient autonomy even more relevant [10]. The concept of patient orientation on which medical rehabilitation is based also emphasizes the importance of respect for patient autonomy [11, 12].

Senin and Meyer [9] distinguish between two levels of patient self-determination in medical rehabilitation: self-determination as an outcome or goal of rehabilitation and self-determination within the rehabilitation measures. This study primarily examines the latter level. A scoping review by Klemmt et al. [13] identified numerous potential aspects, that can promote or endanger patient autonomy in rehabilitation, in the international research literature. These aspects concern both the personal level (patients, professionals, third parties) and the structural levels of rehabilitation clinics and of the health care system. For example, aspects that endanger autonomy have been reported regarding standardization and treatment goals [14], therapeutic measures [15], inadequate qualification and sensitization of professionals [16] or regarding misconceptions of the patients themselves [17]. Autonomy-promoting aspects were identified, for example, in relation to an autonomy-adapted institutional culture [18], supporting patient involvement (e.g. through shared decision making) [19] or the characteristics of the relationship between patients and professionals [20]. There is a lack of empirical evidence regarding autonomy-related rehabilitation practice in the context of the German rehabilitation system. The autonomy-related objectives of medical rehabilitation can benefit from the knowledge gained in this study, as empirical findings regarding patient autonomy in the German setting of inpatient medical rehabilitation are generated for the first time in this study.

The aim of the study is to determine the current state of respecting patient autonomy in inpatient medical rehabilitation practice in Germany and to identify barriers and promoting factors from the perspective of relevant groups. Based on the empirical findings and normative-theoretical considerations, consensual recommendations for the practice of respecting the autonomy of patients will be derived with the involvement of experts.

The research questions are:

What is the current state regarding the implementation of respect for patient autonomy in rehabilitation practice? Are there diagnosis-specific differences?How do the groups involved perceive patient autonomy?To what extent are there difficulties in implementing the principle of respect for autonomy?Can best-practice approaches for respecting patient autonomy be identified?

## Methods

### Study design

A multi-center, prospective, cross-sectional study is being conducted. As different accesses and data types are required to answer the research questions, a multi-method study design is chosen. Firstly, 1) interviews will be conducted with patients to examine the subjective experiences and attitudes of the target group. In addition, 2) interviews will be conducted with professionals to determine the perspectives of the relevant professional groups. This is followed by 3) a written survey of medical directors to investigate clinic-related and organizational characteristics. Subsequently, 4) validation workshops will be held to validate the empirical results from study parts 1–3 in a participatory manner. Finally, 5) the derived practical recommendations are consented in a Delphi process with experts and practitioners (see Fig. 1). The study was registered with the German Clinical Trials Registry (ID: DRKS00035893).

**Fig. 1 Fig1:**
[figure not shown]
Study design

#### Interviews with patients

##### Sampling and recruitment

The recruitment of patients is carried out via eight cooperating rehabilitation clinics in different regions in Germany. The initial approach of the patients is carried out by employees of the cooperating rehabilitation clinics according to predefined inclusion and exclusion criteria. Patients who want to take part in the study and meet the inclusion criteria are then contacted by members of the project team. Inclusion criteria are: written consent to participate in the study, completion of a rehabilitation stay for a maximum of four weeks, rehabilitation in one of the most common diagnostic groups (orthopedics, psychosomatics/psychotherapy, oncology, cardiology, neurology, internal medicine [2]). Exclusion criteria are: insufficient knowledge of the German language, inability to give consent and being underaged. The aim is to contrast the sample regarding the following characteristics: age, gender and diagnostic groups. The aim is to interview four patients for each of the six most common diagnostic groups mentioned above (*n* = 24). If data saturation is not likely after the targeted interviews, further interviews will take place.

The aim is to achieve a sample size of n = 24 interviews (four cases per diagnostic group mentioned above).

##### Data collection

Data is collected by means of narrative individual interviews [21], either by telephone or video conference, depending on the participants' preference. A semi-structured interview guide and a short questionnaire on socio-demographic and health-related characteristics are used. The interviews will be conducted by a member of the project team who has been trained in conducting interviews in advance. Each interview is expected to last 45–60 min. The topics of the interviews are the subjective experience of autonomy during rehabilitation as well as perceived risks of endangerment. The interviews will be audio-recorded and transcribed verbatim.

##### Data analysis

The anonymized transcripts are analyzed using reconstructive hermeneutic text analysis [22]. The analysis is carried out by a member of the project team using MaxQDA software. (Interim) results are discussed by the entire project team. Socio-demographic information is aggregated and analyzed descriptive-statistical.

#### Interviews with professionals

##### Sampling and recruitment

The professionals are also recruited via the eight cooperating rehabilitation clinics. The initial approach is made via the medical directors according to predefined inclusion and exclusion criteria. Professionals who want to take part in the study and meet the inclusion criteria are then contacted by members of the project team. Inclusion criteria are: employment in a cooperating rehabilitation clinics, members of a profession who may come into contact with autonomy-associated constellations in the course of their work (physicians, physiotherapists and exercise therapists, nutritional therapists, occupational therapists, psychologists, social workers and nurses), working in one of the most common main diagnostic groups (orthopedics, psychosomatics/psychotherapy, oncology, cardiology, neurology, and internal medicine [2]), At least 1 year of professional experience in the current position. Exclusion criteria are: insufficient knowledge of the German language. The aim is to contrast the sample regarding the following characteristics: age, gender, professional experience. The aim is to interview three professionals for each of the six most common diagnostic groups mentioned above (*n* = 21). If data saturation is not likely after the targeted interviews, further interviews will take place.

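### Three professionals in each of six diagnostic groups makes 18 interviews, not the stated 21; the plan must say whether the quota runs by diagnostic group or, as seems likely, by profession

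*Protocol article*

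**What the plan says.** The section on interviews with professionals (Sampling and recruitment) gives rule and total in one sentence: "three professionals for each of the six most common diagnostic groups mentioned above (*n* = 21"). The abstract repeats the total: "interviews with professionals (*n* = 21").

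The same section lists the six diagnostic groups as "orthopedics, psychosomatics/psychotherapy, oncology, cardiology, neurology, and internal medicine". It also lists the eligible professions: "physicians, physiotherapists and exercise therapists, nutritional therapists, occupational therapists, psychologists, social workers and nurses". Both lists are inclusion criteria. Of the two, only the diagnostic groups are tied to a number.

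The variation sought within the sample is described separately: "The aim is to contrast the sample regarding the following characteristics: age, gender, professional experience". Neither profession nor diagnostic group is among these characteristics. More interviews may follow if saturation looks unlikely, but only once the targeted ones are done.

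The matching sentence for patients reads: "The aim is to interview four patients for each of the six most common diagnostic groups mentioned above (*n* = 24").

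**The concern.** The sentence gives a rule and a total, and the rule does not produce the total. Whoever recruits has to decide which of the two to follow.

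The difference goes beyond three interviews. In a purposive qualitative sample the quota is the design, because it decides whose views are heard. A quota by diagnostic group serves the first research question in the Background, which asks about differences between diagnoses. A quota by profession serves the purpose given under Study design, where this part is meant to gather the views of the professions concerned. Each rule leaves the other dimension unprotected.

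Under the written rule, profession is only an eligibility criterion, so all cells can be filled without, for example, a nurse or a social worker. Uneven coverage is a realistic possibility: the Background describes rehabilitation teams as strongly dominated by medicine, and the first approach to staff goes through the medical directors. A gap here would carry forward, because the directors' survey questionnaire is built on the findings of the two interview parts.

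**Working it through.** **Inputs**, all from the protocol article:
- interviews per stratum, professionals: 3
- diagnostic groups listed: 6
- profession entries as printed: 7 (physicians; physiotherapists and exercise therapists; nutritional therapists; occupational therapists; psychologists; social workers; nurses)
- cooperating clinics: 8 ("The professionals are also recruited via the eight cooperating rehabilitation clinics")
- stated total: 21, in the sampling section and in the abstract
- patients: 4 per group, 6 groups, stated total 24

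**Formula:** target = interviews per stratum × number of strata.

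**Control.** Patients: 4 × 6 = 24, as stated. The article's notation therefore gives an exact product in the parallel sentence.

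**Stated rule for professionals.** 3 × 6 = 18, against 21. The difference is 21 − 18 = 3, and 3/21 = 14%.

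**Which stratum would give 21?**

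| Stratum | Number | 3 × number | 21 / number |
|---|---|---|---|
| Diagnostic groups | 6 | 18 | 3.5 |
| Professions as listed | 7 | 21 | 3 |
| Professions, physiotherapists and exercise therapists split | 8 | 24 | 2.625 |
| Clinics | 8 | 24 | 2.625 |

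Only the seven profession entries reproduce the total. Keeping six diagnostic groups and changing the number per group does not help, since 3.5 is not a whole number.

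**Saturation clause.** It applies after the targeted interviews, so it cannot account for the extra 3 within the target.

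**Assured interviews per profession.** Under the written rule this is 0 for each of the seven, because no named profession is tied to any cell. Under three per profession it is 3 for each, and diagnostic group would then have no assured minimum unless one is stated.

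**The case against.** **Three as a minimum.** If three is read as a floor for each group, 21 interviews satisfy both figures: 18 in the cells and 3 unallocated. This is possible. The sentence does not say at least, however, and its twin for patients is an exact product, so it is the less natural reading. Even then the article does not say where the other three go.

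**The diagnostic-group quota may be intended.** The first research question asks about diagnoses, the Discussion expects differences between diagnostic groups, and no research question compares professions. This stands. A reader might infer from 3 × 7 = 21 that the written quota is simply wrong and was meant per profession. The documents do not support going that far: no per-profession quota is stated anywhere, and the match depends on counting physiotherapists and exercise therapists as one entry.

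**The consequence is limited.** A reader might also infer that the study would lose its ability to report by profession. No such reporting is planned; the analysis is a content-structuring qualitative content analysis. What is at stake is coverage. No power, error rate or estimate depends on 18 versus 21, and the target is an aim that may be extended for saturation. That softens the practical effect but does not remove the contradiction.

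**Condensed article.** Finer selection rules may stand in the full protocol. That would excuse missing detail, but here rule and total are both printed and they conflict.

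**Conclusion.** The point holds: the stated quota gives 18 interviews and the stated total is 21, a gap of 3 (14% of 21). This rests on nothing beyond the printed numbers and on reading three as the number per group, as the patient sentence supports.

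That the quota was meant per profession is probable but not established. It rests on three things: the exact 3 × 7 match with professions counted as printed, the same total appearing in the abstract, and the near-identical wording of the patient sentence, which suggests carry-over. The research question on diagnoses points the other way. Only the authors can settle it.

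The error is small in number. It still deserves correction because the stratum determines which coverage is secured in a part of the study that shapes the later questionnaire.

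**What to change.** State the intended stratum in the professionals' sampling section and make the abstract agree with it. Either:

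1. three from each of the seven professional groups as listed, n = 21, with diagnostic group added to the contrast characteristics; or
2. three from each of the six diagnostic groups, n = 18 in both places, with profession added to the contrast characteristics.

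If three is meant as a minimum per diagnostic group, say so and state how the remaining 3 of the 21 are allocated. If interviews have already begun, state the rule that was actually used.

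The cost is a few words in two places. Neither option needs an interview beyond the stated 21.

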##### Data collection

Data is collected by means of problem-centered individual interviews [23], either by telephone or video conference, depending on the participants' preference. A semi-structured interview guide and a short questionnaire on socio-demographic and job-related characteristics are used. The interviews will be conducted by a member of the project team who has been trained in conducting interviews in advance. Each interview is expected to last 45–60 min. The topics of the interviews are perceptions of patient and professional autonomy. The interviews will be audio-recorded and transcribed verbatim.

##### Data analysis

The anonymized transcripts are analyzed using content analysis according to the content-structuring qualitative content analysis method [24]. The analysis is carried out by a member of the project team using MaxQDA software. (Interim) results are discussed by the entire project team. Socio-demographic information is aggregated and analyzed descriptive-statistical.

#### Survey of medical directors

##### Sampling and recruitment

Included are all inpatient rehabilitation clinics of all diagnostic groups, treating persons of legal age in Germany that are operated by the German Pension Insurance (n = 900 [25]). Rehabilitation clinics dealing with the diagnostic groups of addiction and rehabilitation of mentally ill people are excluded. The medical directors are contacted by email via the German Pension Insurance and are invited to participate in the study. For this purpose, links/QR codes to the survey are sent in these emails.

##### Data collection

The survey is conducted using a self-constructed questionnaire based on the findings of 1) and 2). This is programmed in the SoSciSurvey program and can be answered online by the respondents. The estimated completion time is 15–20 min. Topics include the current status of respect for patient autonomy and wishes and needs from the perspective of the rehabilitation clinics.

##### Data analysis

The aggregated data from the survey is first checked for correctness and plausibility. The analysis is initially carried out descriptively by calculating frequencies and positional measures. Free text responses are categorized. Group comparisons are calculated using t-tests or chi2-tests, Eta-square coefficients or the correlation coefficient according to Bravais-Pearson, depending on the scale level of the variables examined. The analysis is carried out using SPSS.

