## Discussion

This study will address an important gap in the current empirical literature by identifying the current state and needs of patients, professionals and medical directors of rehabilitation clinics regarding the practice of respecting patient autonomy in inpatient medical rehabilitation in Germany. Based on the empirical findings and normative-theoretical considerations, consensual recommendations for the practice of respecting the autonomy of patients will be derived with the involvement of experts. We thus expect that the study output will be of interest to a wide range of knowledge users including scientists, stakeholders, professionals, patient groups and clinic representatives. We also expect that the results can contribute to coming closer to the ideal of respect for patient autonomy in rehabilitation practice, e.g. by identifying barriers and promoting factors.

Expected results could concern organizational/institutional, structural as well as personal or relationship aspects. We suspect that there may be a gap between self-determination as an objective or outcome of rehabilitation and respect for patient autonomy during the inpatient stay. We also suspect that there may be differences in terms of diagnostic groups (e.g. neurology vs. orthopedics).

The strengths of the study are that the relevant groups and perspectives are included. In addition, the surveys are multi-center and cross-indication, which means that bias potential can be avoided. The multi-method approach means that the research questions can be adequately addressed in each case. Challenges could relate to the response to the medical directors' survey. In addition, before starting the empirical surveys, a theoretical-normative classification of the theoretical construction of patient autonomy in medical rehabilitation must be carried out to be able to clearly define the topic of the study. This is done through extensive literature research.

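### Uncorrected eta-square, the listed statistic that fits a metric rating across several groups, overstates association by an amount that depends on the number of groups and responders; a bias-corrected coefficient with an interval would be a cheap improvement

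*Protocol article*

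**What the plan says.** The Data analysis section for the survey of medical directors begins with descriptive statistics and then lists, for group comparisons, t-tests, chi-square tests and "Eta-square coefficients or the correlation coefficient according to Bravais-Pearson, depending on the scale level of the variables examined". It names no grouping variable, no cut-off for eta-square, no ranking of variables, no analysis of variance and no bias-corrected coefficient.

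Three other places bear on how eta-square would be used:

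- The research questions at the end of the Background ask: "Are there diagnosis-specific differences". The Discussion adds that the authors suspect such differences.
- The survey's Sampling and recruitment section is broad: "Included are all inpatient rehabilitation clinics of all diagnostic groups, treating persons of legal age in Germany". It puts the number of clinics at 900 and excludes two diagnostic areas. It does not say how many diagnostic categories the analysis will use. The Background names six most frequent fields.
- No expected response is given. The Discussion says only: "Challenges could relate to the response to the medical directors' survey".

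**The concern.** The listed statistics divide by scale level. A t-test takes two groups, a chi-square test takes categorical outcomes, and the Pearson correlation takes two metric variables. For a metric rating across three or more nominal groups, eta-square is what remains. It is a fair inference, though not a statement of the article, that it would summarise how ratings differ by diagnostic group.

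Eta-square is the between-group share of the total sum of squares. Sampling variation alone makes group means differ, so the coefficient cannot centre on zero when the groups are equal. The excess grows with the number of groups and shrinks with the number of responders. Two things are at stake:

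- A reader may take a small positive value as a modest association when it is about what chance would give.
- Coefficients for variables with different numbers of categories, such as diagnostic group against a two- or three-level clinic feature, are not on an equal footing.

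The survey results pass into a validation workshop and then into the recommendations put to the Delphi panel, so the size of these coefficients may be read for meaning.

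**Working it through.** The article gives no eta-square value, threshold or sample-size calculation, so there is no figure of its own to reproduce.

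**Inputs**

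- Number of clinics invited: 900 (survey, Sampling and recruitment).
- Number of groups k: not stated for the survey. Assumed k = 6, after the six most frequent fields in the Background, with k = 10 as a larger case.
- Response: not stated. Assumed range 5% to 100%, so N = 45 to 900.
- Threshold 0.06: illustrative only, not from the article.

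**Step 1: no true difference.** With normal errors, eta-square follows a Beta((k−1)/2, (N−k)/2) distribution, with mean (k−1)/(N−1). For k = 6 and N = 900 this is 5/899 = 0.0056.

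| Response | N | Null mean, k = 6 | 95th percentile, k = 6 | P(eta-square > 0.06), k = 6 | Null mean, k = 10 |
|---|---|---|---|---|---|
| 100% | 900 | 5/899 = 0.0056 | 0.012 | about 0 | 0.010 |
| 50% | 450 | 5/449 = 0.011 | 0.025 | about 0 | 0.020 |
| 30% | 270 | 5/269 = 0.019 | 0.041 | 0.6% | 0.034 |
| 20% | 180 | 5/179 = 0.028 | 0.061 | 5.4% | 0.050 |
| 10% | 90 | 5/89 = 0.056 | 0.122 | 38% | 0.101 |
| 5% | 45 | 5/44 = 0.114 | 0.240 | 78% | 0.205 |

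**Step 2: a real difference.** The bias falls to about (1 − eta²)(k−1)/(N−1). For N = 90, k = 6 and a true value of 0.14 this gives 0.86 × 0.0562 = 0.048. A simulation of 3,000 runs with equal group sizes gave 0.0475.

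**Step 3: corrected coefficients.** Epsilon-square is 1 − (1 − eta²)(N−1)/(N−k). Omega-square is (SSB − (k−1)·MSW)/(SST + MSW), where SSB and SST are the between-group and total sums of squares and MSW is the within-group mean square. In the same simulation with k = 6:

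- No true difference: both averaged about 0.000 at every N tried, from 45 to 900.
- True value 0.06:

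| N | Eta-square | Epsilon-square | Omega-square |
|---|---|---|---|
| 900 | 0.065 | 0.060 | 0.060 |
| 180 | 0.085 | 0.059 | 0.058 |
| 90 | 0.112 | 0.060 | 0.059 |

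**Step 4: test error.** The F-test on the same sums of squares rejected in 4.7% to 5.1% of the null runs. The bias lies in the size of the coefficient and does not affect the test.

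**Step 5: comparing variables.** The coefficients were drawn independently.

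- If neither variable matters, an 8-category variable shows the larger eta-square than a 3-category one in 91% of comparisons. This hardly depends on N.
- At N = 270, a null 8-category variable exceeds a 3-category variable truly explaining 2% of variance in 50% of comparisons with eta-square, and in 18% with omega-square.
- Against a real 2-category effect of 0.06, a null 10-category variable has the larger eta-square in 0% of draws at N = 900, 37% at N = 180 and 70% at N = 90.

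**The case against.** Eta-square is a standard descriptive effect size, and a condensed article may leave refinements to a fuller plan. All eligible clinics are invited, so eta-square can be read as describing those clinics and not as estimating something beyond them. At the stated 900 with six groups the null mean is only 0.0056. Larger figures need a low response or more groups, and both are assumptions.

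Much of this stands, and it limits the severity. The descriptive reading protects the coefficient fully only if every clinic answers. With 30% responding at random, the null mean among responders is 0.019 against 0.0056 for the full set, a gap of 0.019 − 0.0056 = 0.013. The 900 is the number invited, and the authors themselves name response as a challenge. The coefficient is also a stated choice and not an omission, so improving it does not amount to asking for detail left elsewhere.

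A reader might infer more: that the survey will report diagnosis effects where none exist, or that it will place many-category variables at the top. The article does not support either. It sets no cut-off and no rule that treats a non-zero value as an effect, and it plans no ranking. The pull towards many categories is also a tendency and not a certainty: among four null variables with 2, 3, 6 and 10 categories, the 10-category one came first in about 77% of draws.

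**Conclusion.** The point holds as a low-severity improvement. Uncorrected eta-square overstates association on average, by (k−1)/(N−1) with no difference and by less with a real one. For six groups that is negligible at full response (0.0056), small at 30% (0.019), and large enough to mislead at roughly 20% or below (0.028 at 20%, 0.056 at 10%). More than six categories would enlarge it. It would be wrong to treat (k−1)/(N−1) as a fixed bias whatever the true effect, or to say that false-positive rates rise.

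The conclusion rests on the inference that eta-square will be applied to diagnostic group or another factor with several levels, on the assumed k and response rates, and on normal errors for the exact distribution.

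**What to change.** In the Data analysis section for the survey of medical directors, replace eta-square with omega-square or epsilon-square, or report one of them beside it. Compute it from the same one-way sums of squares, give a 95% confidence interval, and state the k and N behind each coefficient. Use the corrected coefficient wherever the strength of association is compared between diagnostic group and other clinic characteristics.

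The cost is one clause of text and an extra output column, with no new data. Reported coefficients will be slightly smaller, and some will be at or below zero. These should be reported as they are and read as no evidence of association. The correction reduces misordering between variables but does not remove it (18% in the N = 270 example), which is why the interval is needed as well.
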